#### Mortality

Overall and cancer-related mortality in either arm after enrolment will be recorded. Mortality (and cause) will be determined using the Demographics Batch Service to access the national electronic database of the UK NHS.

#### Use of stoma after colorectal surgery

Use of stoma (either temporary or permanent if this notification is available) will be recorded.

#### Inpatient and critical care occupancy

A record will be made of inpatient and critical care occupancy associated with interventions; data will inform planning of economic evaluation in any subsequent randomised trial.

#### Quality of life

Quality of life (QoL) will be assessed using the European Organisation for Research and Treatment of Cancer Core Quality of Life (EORTC QLQ-C30) and colorectal cancer liver metastasis specific module (EORTC QLQ-LMC) questionnaires, which have been validated for assessment of patient-reported outcomes during treatment of colorectal liver metastases.^33^ The questionnaire will be completed by patients at time of enrolment and at 12 and 24 months. The EuroQoL questionnaire with 5 dimensions with 3 levels of severity (EQ-5D-3L)^34^ will also be completed at the same time points, again supporting the design of future trial-based economic analyses.

#### Qualitative study interview guide

Structured interviews will last approximately 45 min, and explore (1) for patients and caregivers: the experience of disease, particularly through the treatment pathway; understanding and expectations of time frame for investigations; how they were informed of the diagnosis; how they received information related to the condition and treatment pathway; the type of information provided and who were the professionals explaining this; the nature and impact of information about diagnosis on patients and caregivers, and on their relationship with the clinician; aspects of the process patients and caregivers found useful/not so useful and what could be improved; and the acceptability of entering into a future randomised control trial; (2) for clinicians: their experience of providing care, in particular, the perspectives and their views on treatment pathways; difficulties and challenges around treatment allocation and decision-making processes; the relationship with patients; acceptability and barriers to entering patients who may be under their care into a future randomised trial; any ethical issues and the potential clinical value of future randomised control study.

### Data sources and measurements

Data will be collected prospectively using electronic study clinical case report forms. These will be anonymised and encrypted for storage and analysed prospectively during study to maximise data completion and resolve emergent problems in a timely fashion. The principal source of data will be the individual patient records. In addition, information will be gained by direct interview with patients (for quality of life assessment) and by interview with clinicians (for MDT choice decisions). Vital status beyond the duration of the study will be determined through the Demographics Batch Service of the NHS. Data will be reported at the end of year 3 allowing for a minimum 12 months outcome data in the entire cohort. It is also proposed (contingent on separate funding) that information on outcome will be collected for up to 5 years from study commencement, providing an informative survival analysis of treatment options.

Qualitative interviews will be audio recorded and transcribed verbatim.

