**Methods and analysis:**

Colorectal cancer with Synchronous liver-limited Metastases: an Inception Cohort (CoSMIC) is an inception cohort study of patients with a new diagnosis of colorectal cancer with synchronous liver-limited metastases. The sequence of treatment received, and factors influencing treatment decisions, will be evaluated against European Society of Medical Oncology guidelines. Clinical data will be collected, and quality of life, morbidity, mortality and long-term outcome compared for different treatment sequences adjusted for prognostic factors. Disease-free survival or progression will be measured at 1, 2 and 5 years. A nested qualitative study will ascertain patient experiences and clinician perspectives on delivery of care.

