### Setting

The study population will comprise patients with colorectal cancer with liver-limited hepatic metastases referred to the Hepatobiliary Surgical Unit at Manchester Royal Infirmary—an NHS regional cancer-network approved hepato-pancreato-biliary (HPB) centre with a formally constituted and National Cancer Network peer-review accredited MDT. The study opened for recruitment in April 2015 with prospective recruitment to be undertaken for 24 months.

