### Study size

Based on clinical registers, the HPB unit at Manchester Royal Infirmary sees approximately 75 patients with colorectal cancer with synchronous liver-limited hepatic metastases per annum. As there are no study-related interventions, recruitment rates should be high and dropout low and is estimated to provide 150 patients in the 2-year recruitment period. A formal power calculation is not provided for this inception cohort study. Instead, the sample size is informed by the need to: provide stable estimates of variance for a range of outcomes; explore the relationship between the treatment pathway and health outcomes; estimate acceptability and recruitment rates; and describe patient and clinician experiences.

Purposeful sampling will be used to select patients from the cohort for the qualitative study. It is estimated that a sample size of four to six patients per group and one to two clinicians will produce data saturation. However, we will continue to interview until data saturation is reached.

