## Dissemination policy

The results of CoSMIC will be presented at the appropriate conferences. Study outcome data will be set at 1, 2 and 5 years. Following publication of the final results, anonymised raw data will be made available.

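### Outcome collection stops 5 years after the study opens, but recruitment takes 24 months, so the stated 5-year disease-free survival or progression cannot be observed for essentially any patient

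*Protocol article*

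**What the plan says.** The timetable is spread over several sections of the protocol article.

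- **Setting:** "The study opened for recruitment in April 2015 with prospective recruitment to be undertaken for 24 months".
- **Study size:** the unit "sees approximately 75 patients with colorectal cancer with synchronous liver-limited hepatic metastases per annum", which is "estimated to provide 150 patients in the 2-year recruitment period".
- **Data sources and measurements:** "Data will be reported at the end of year 3 allowing for a minimum 12 months outcome data in the entire cohort". The next sentence proposes, conditional on separate funding, that "information on outcome will be collected for up to 5 years from study commencement". The same section says that vital status after the study ends will be traced through the NHS Demographics Batch Service. That statement carries no funding condition.
- **Abstract (Methods and analysis):** "Disease-free survival or progression will be measured at 1, 2 and 5 years".
- **Data collection, Box 1:** disease-free survival and disease progression are listed under outcomes at 1, 2 and 5 years.
- **Dissemination policy:** "Study outcome data will be set at 1, 2 and 5 years".
- **Quality of life:** "The questionnaire will be completed by patients at time of enrolment and at 12 and 24 months".

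None of the three places that list a 5-year outcome mentions the funding condition or the calendar cut-off.

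**The concern.** The end of collection is fixed in calendar time from the opening of the study, while the outcomes are patient-level times. With two years of staggered entry, the two cannot both hold at 5 years: a patient who enters in the last month of recruitment has only about three years before collection stops.

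At stake is the long-term half of the study's second aim, comparable outcome data by treatment sequence. A reader of the abstract will expect disease-free survival or progression at 5 years, possibly split by synchronous, liver-first and bowel-first routes. The stated window would leave almost nobody under observation at that time in any of the three groups.

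**Working it through.** **Inputs.** Recruitment from month 0 (April 2015) to month 24 (April 2017), from Setting. About 75 patients a year, from Study size. First report at month 36 (April 2018) and end of outcome collection at month 60 (April 2020), from Data sources and measurements. Stated outcome times of 12, 24 and 60 months, from the abstract, Box 1 and Dissemination policy.

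**The plan's own figures reproduce.**

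- Sample size: 75 × 2 = 150.
- Minimum follow-up at cut-off C is C - 24. At the year-3 report, 36 - 24 = 12 months, as stated.

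**Follow-up at the end of collection.** At C = 60 the last entrant has 60 - 24 = 36 months and the first has 60 - 0 = 60 months. The range is therefore 36 to 60 months, with mean 48 under uniform accrual.

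**Share reaching f months by cut-off C.** A patient qualifies only if enrolled by month C - f. Under uniform accrual the share is (C - f)/24, kept between 0 and 1. These are counts of potential follow-up out of 150, before deaths and dropout:

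| Cut-off (month) | Range of follow-up (months) | Reach 24 | Reach 36 | Reach 48 | Reach 60 |
|---|---|---|---|---|---|
| 36 | 12–36 | 75 | 0 | 0 | 0 |
| 48 | 24–48 | 150 | 75 | 0 | 0 |
| 60 | 36–60 | 150 | 150 | 75 | 0 |
| 72 | 48–72 | 150 | 150 | 150 | 75 |
| 84 | 60–84 | 150 | 150 | 150 | 150 |

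A zero at the upper end of a range means nobody except a patient enrolled on day 0.

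**Dependence on accrual.** For 60 months at C = 60, the enrolment deadline is month 0. The share is therefore 0% under uniform accrual, under a linear ramp-up, where the cumulative share enrolled by month t is (t/24)², and under front-loading, 1 - (1 - t/24)².

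**Allowing an early 5-year assessment.** Under uniform accrual, accepting it 3 months early gives 3/24 × 150 = 18.75, about 19 patients (12.5%). Accepting it 6 months early gives 6/24 × 150 = 37.5, about 38 (25%). For the 3-month allowance, ramp-up gives about 2 patients and front-loading about 35.

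**The 24-month data.** At month 36 the share with 24 months is 12/24 = 50% under uniform accrual, (12/24)² = 25% under ramp-up and 1 - (1 - 12/24)² = 75% under front-loading. All 150 have reached 24 months only at 24 + 24 = month 48 (April 2019).

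**The case against.** The strongest replies are these.

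- **Mortality is covered separately.** Vital status beyond the study comes from the Demographics Batch Service, and the Mortality section uses it for cause of death as well. This stands. A reader might infer that every 5-year outcome is lost, but the documents do not support that for overall survival. The service is not described as giving recurrence or progression, so the point remains for those outcomes.
- **Censored data are usable.** A time-to-event analysis can use 36 to 60 months of follow-up and gives complete 3-year information. That is true, but almost nobody would be at risk at 60 months, so a 5-year estimate would have almost no support.
- **An article leaves visit windows to the full protocol.** That is fair, and a window would raise the count above zero. Even a 6-month allowance reaches only a quarter of the cohort under uniform accrual.
- **Commencement may have been meant as each patient's entry.** If so, the conflict disappears. But the text refers to the study's commencement, whereas treatment times and dropout are counted in days from enrolment, and the disease-free survival heading is likewise tied to enrolment.
- **Little depends on it formally.** The cohort has no power calculation, its modelling is exploratory and its reporting is described as descriptive. This stands and limits the severity.

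Two further inferences are tempting and should not be drawn. One is that the year-3 report is wrong because many patients will lack 24-month data. That report offers only a 12-month minimum, no section promises 2-year results in it, and the share affected depends on the accrual pattern. The other is that 24-month quality of life depends on the extra funding. The condition is attached to the proposed collection up to 5 years, and nothing says that the 24-month questionnaires stop at year 3.

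**Conclusion.** The point holds for disease-free survival and progression. As written, the collection window excludes the 5-year outcome that three other places in the article state without qualification. Potential follow-up at closure is 36 to 60 months, and essentially none of the 150 patients reaches 60 months. That result does not depend on the accrual assumption. It rests on reading the 5 years as running from the study's opening, on recruitment taking the stated 24 months, and on an exact 5-year assessment.

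It is an internal contradiction in the stated horizon. No sample size, test or decision rule turns on it. Five-year overall survival may still be obtained from vital status. The year-3 report is consistent with its own stated minimum. It is only worth recording that 24-month outcomes and quality of life will be complete for every patient from month 48 onwards.

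**What to change.** Choose one of two routes.

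1. **Keep the 5-year outcome.** In Data sources and measurements, define the window as 5 years from each patient's enrolment, so that collection for the last patient ends about April 2022 (month 84). The cost is two further years of record-based recurrence follow-up, under the same separate funding. This is more than a registry download, because the definition of disease-free rests on CT and, for watch-and-wait patients, on endoscopic and clinical evidence too.
2. **Keep the April 2020 cut-off.** State that 3 years is the last time point complete for the whole cohort for disease-free survival or progression, and limit 5-year results to overall survival from vital status. Amend the abstract, Box 1 and Dissemination policy to match. The cost is wording only, with a shorter stated horizon.

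Under either route, state the funding condition wherever 5-year outcomes are listed. The year-3 report needs no correction. A sentence saying that complete 24-month outcomes and quality of life are available only from month 48 (April 2019) would prevent misreading.

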### Study size

Based on clinical registers, the HPB unit at Manchester Royal Infirmary sees approximately 75 patients with colorectal cancer with synchronous liver-limited hepatic metastases per annum. As there are no study-related interventions, recruitment rates should be high and dropout low and is estimated to provide 150 patients in the 2-year recruitment period. A formal power calculation is not provided for this inception cohort study. Instead, the sample size is informed by the need to: provide stable estimates of variance for a range of outcomes; explore the relationship between the treatment pathway and health outcomes; estimate acceptability and recruitment rates; and describe patient and clinician experiences.

Purposeful sampling will be used to select patients from the cohort for the qualitative study. It is estimated that a sample size of four to six patients per group and one to two clinicians will produce data saturation. However, we will continue to interview until data saturation is reached.

### Analysis plan

The care of patients within the study pathway will be characterised by their principal treatment route as synchronous, liver first or bowel first. All patients will provide outcomes which will be included within analyses, grouped according to the treatment sequence received. Complication profiles in patients according to treatment group will be reported.

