#### Timelines for completion of the treatment protocol

For the purposes of this study, this is defined as the amount of time in days from enrolment to completion of the protocol. The term ‘protocol’ relates to completion of the common treatment pathway.

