#### Failure to complete the treatment protocol

This is defined as dropout prior to completion of the allocated treatment sequence. It will be further categorised as due to disease progression, patient choice or unrelated to colorectal cancer (for example myocardial infarction) and will be recorded as the time in days from enrolment.

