#### Disease-free survival 12 months after enrolment into protocol

This is defined as the absence of tumour on a CT scan of the thorax, abdomen and pelvis undertaken at the completion of the protocol. In the case of those patients with rectal tumours treated by a’ watch and wait ‘policy, the term disease free can only be applied if there is a combination of radiological, endoscopic and clinical evidence of absence of cancer.

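### Outcomes timed from enrolment are grouped by the treatment sequence received: unresected patients have no group, and the sequence comparison can be biased by an amount and in a direction that the rule leaves open

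*Protocol article*

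**What the plan says.** *Analysis plan* fixes the grouping. Care is "characterised by their principal treatment route as synchronous, liver first or bowel first", and then: "All patients will provide outcomes which will be included within analyses, grouped according to the treatment sequence received". No category is named for a patient who has no resection, or only one of two planned operations.

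The outcome clocks start at enrolment. Time to completion is "the amount of time in days from enrolment to completion of the protocol". The disease-free outcome is headed "Disease-free survival 12 months after enrolment into protocol", although its definition reads a CT scan taken when the treatment protocol is completed. *Mortality* is recorded after enrolment.

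Failure before completion is expected. *Failure to complete the treatment protocol* says: "This is defined as dropout prior to completion of the allocated treatment sequence". The same section sets out reasons and timing: "due to disease progression, patient choice or unrelated to colorectal cancer (for example myocardial infarction) and will be recorded as the time in days from" (the clock again starts at enrolment). *Recruitment* also admits patients whose pathway has already begun, typically after an acute presentation from the bowel tumour. The MDT's choice is to be collected "by interview with clinicians (for MDT choice decisions").

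**The concern.** Group membership depends on what happens after the clock starts. A patient must stay alive and operable long enough to be operated on before any sequence has been received. Patients who do not reach surgery fall outside all three routes, and their bad outcomes are then either dropped or assigned by a rule the plan does not give. If staged patients are classified only after the second operation, the staged groups are also cleared of everyone who fails in between.

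Outcome data comparing synchronous with sequential surgery are a primary aim. The abstract promises a comparison of sequences adjusted for prognostic factors and says the results may feed into a definitive trial. The tools named in *Statistical methods*, generalised linear models and propensity score matching, balance characteristics known at baseline. Surviving to surgery is not one of them, so they cannot correct this. *Acknowledgement of selection bias* covers patients who are never referred, not those who fail after enrolment.

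**Working it through.** **The plan's own figure.** *Study size* gives about 75 patients a year for 2 years: 75 × 2 = 150. This reproduces and is not in dispute. The article states no power, alpha or effect size.

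**Can every patient be placed?** Eligibility requires performance status 0 to 2 and suitability for chemotherapy, not resection. The pathway under *Aims of the study* includes early neoadjuvant chemotherapy, and failure through progression is foreseen. A patient who progresses on chemotherapy and is never operated on is included by one half of the grouping sentence and has no place under the other half.

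**What does the rule do when sequences are truly equal?** Inputs not in the document, so assumed: an exponential event-free curve with a 12-month median, identical in all groups; synchronous surgery at month 3; staged surgery complete at month 7; patients who fail before classification are in no group.

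S(t) = 0.5^(t/12), so true S(12) = 0.500 everywhere. Among patients classified at month w, the 12-month figure is S(12)/S(w).

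| Staged patients classified at | Synchronous | Staged | Gap (staged minus synchronous) |
|---|---|---|---|
| Second operation, month 7 | S(12)/S(3) = 0.595 | S(12)/S(7) = 0.749 | +15 points |
| First operation, month 3 | 0.595 | S(12)/S(3) = 0.595 | 0 |
| First operation, already done at enrolment | 0.595 | S(12)/S(0) = 0.500 | about −9 to −10 points |

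On the completed-sequence reading, the gap is 7 to 25 points if staged surgery completes at month 5 to 9. It is 6 to 29 points if the median is also varied from 9 to 18 months.

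**Scaled to the document's survival figures.** *Background* gives 5-year survival of 25% to 40% for resectable liver-only disease. Take constant death hazards from these, S(t) = S5^(t/60), and assume patients are split equally between intended synchronous and intended staged surgery, with the synchronous operation at month 3. A null simulation of 600,000 patients gave:

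- *Completed sequence, second operation at month 9:* 12-month survival 0.81 to 0.87 (synchronous) against 0.93 to 0.96 (staged). The spurious staged-to-synchronous death-rate ratio is about 0.33 over 12 months and 0.69 to 0.70 over 24 months. With the second operation at month 6, the ratios are about 0.66 and 0.83 to 0.84.
- *First operation, equal waits of 3 months:* ratio about 1.0.
- *First operation, bowel surgery already done at enrolment:* ratio about 1.35 to 1.37, against staged surgery.

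**Patients without a group, out of 150.** First-operation rule with equal waits: 150 × (1 − 0.40^(3/60)) = 6.7 and 150 × (1 − 0.25^(3/60)) = 10, so about 7 to 10. Completed-sequence rule: 75 × (1 − S(3)) + 75 × (1 − S(w)), which is about 10 (40%, w = 6) to 23 (25%, w = 12). At the 6% quoted for stage IV overall, the counts are about 20 and 28 to 42. These count deaths only; patients who progress and are never resected would add to them.

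**Grouping by intention.** Under the same null, 12-month survival is equal in both groups (0.76 and 0.76 at 25%; 0.83 and 0.83 at 40%), and all 150 patients have a group.

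**The case against.** The best defence is that the staged labels name the first operation, so a patient could be classified then. With equal waits the between-group bias is then close to nil. That stands, and it is why a reader who infers a demonstrated 15-point bias in favour of staged surgery goes too far. That figure needs classification at the second operation and exclusion of earlier failures, whereas the plan says everyone is included. The waits and the median are also assumed, and the illustration is a time-to-event curve, not the protocol's CT-based definition. The unresected patients still have no group on either reading.

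A reader might also infer that the article holds two conflicting definitions of exposure, because failure is measured as "dropout prior to completion of the allocated treatment sequence". It does not: a process outcome about non-completion has to refer to the plan. Nor does anything say that an emergency bowel operation moves a planned liver-first patient to bowel-first; the article records such surgery as morbidity.

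As-received grouping is natural for complications, margins and length of stay, which exist only after surgery. The modelling is labelled exploratory, and reporting is called pragmatic and descriptive. Landmark or time-varying methods could sit in an analysis plan that is not shown. These points lower the severity. They do not remove the problem, because the article itself fixes the grouping rule and promises an adjusted comparison.

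**Conclusion.** The point holds and should be fixed. Established from the text: groups are set by surgery received while outcomes run from enrolment, only surgical routes are named, patients who fail before any resection have no group, and the named adjustment methods do not correct this.

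Not established: the size or direction of the resulting bias. Both depend on whether received means the first operation or the completed sequence, and on waits the document does not give. Under a null with assumed waits, the artefact runs from near nil (first operation, equal waits) to about 15 points at 12 months in favour of staged surgery (completed sequence, 12-month median, months 3 and 7). It can reverse when bowel surgery precedes enrolment. An observed difference between sequences could therefore not be interpreted.

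**What to change.** For survival, progression and quality-of-life comparisons, make the main grouping the sequence intended at the first HPB MDT decision: liver-first, bowel-first, synchronous, or no resection planned or decision deferred. Count every enrolled patient in that group from that date, whether or not surgery follows.

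Identify patients whose bowel surgery preceded enrolment. Analyse them separately or with delayed entry, since starting the clock at the MDT decision does not by itself deal with them.

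Keep sequence received as a secondary grouping. State whether it means the first operation or the completed sequence, add an explicit category for no or incomplete resection, and use a landmark or a time-varying exposure. Keep it also for perioperative outcomes such as complications, margins and stay.

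The cost is analysis wording and one field for MDT intention; the MDT's choice is already to be collected, and no care changes. The drawback is that the contrast becomes one of intended strategies, diluted where patients switch.
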